**Method::**

This study will use a two-armed, parallel, assessor-blinded randomized controlled trial design and will be conducted in the Daejeon Jaseng Hospital of Korean Medicine in South Korea. One hundred twenty patients will be recruited and randomized into an integrative Korean medicine treatment (IMKT) + NRT group and IMKT group in a 1:1 ratio. The primary outcome is a change in the numeric rating scale for neck pain immediately after treatment on hospital day 5 compared to those at baseline. The secondary outcomes are numeric rating scale for radiating arm pain, visual analogue scale for neck pain and radiating arm pain, cervical active range of motion, neck disability index, Patient Global Impression of Change, Short Form-12 Health Survey, and Posttraumatic Stress Disorder Checklist for DSM-5.

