#### Experimental group: IKMT + NRT

2.3.1

For the experimental group, four sessions of NRT will be administered from hospital day 2 to 5, and IKMT will be administered daily. Each session of NRT will last for about 10 minutes.

During the NRT, the patient will be seated, and the therapist will apply pressure to the cervical treatment point while firmly supporting the patient's head and progressively extending the neck to move the joint. The therapist will apply pressure to the posterior neck with the thumb and other fingers while supporting the occipital region with the dorsum of the hand.

With the patient seated on a chair, the therapist will place the thumb and index finger on the areas around the articular pillar in the upper cervical region with tense muscles or on the acupoints GB20, BL10, GB21, or SI15; support the back of the patient's head with the 1^st^ and 2^nd^ metacarpal bone; and place the other hand on the patient's forehead. Then, light flexion and extension will be repeated within the ROM of the cervical spine without pain. The weight of the patient's head will add weight to the hand supporting the head and, thus, will transfer pressure to the thumb and index finger, and compression and relaxation will be repeated based on the transferred pressure. During the treatment, the therapist will comfort the patient by assuring them that the treatment does not cause pain so that the patient can relax the neck muscles. Once the targeted area is adequately flexed and extended over a sufficient period of time, the pressure points will be moved to the central and lower neck to repeat the procedure. The range of cervical extension increases at the lower neck area (Figure S1, Supplemental Digital Content).

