### Participant timeline

2.6

At the screening visit, the participants will be enrolled after signing a written consent form, and those who qualify per the inclusion/exclusion criteria will proceed with the trial. The detailed timeline is shown in Table 1.

**Table 1 T1:** Schedule of study.

Time point	Study period						
	Screening	Active treatment				Follow-up	
	Day 1 (visit 1)	Day 2 (visit 2)	Day 3 (visit 3)	Day 4 (visit 4)	Day 5 (visit 5)	Discharge (visit 6)	12 wks (visit 7)
Enrolment							
Eligibility screening	○						
Written informed consent	○						
Sociodemographic hic characteristics	○						
Information about accident	○						
Randomized allocation		○					
Credibility and expectancy questionnaire		○					
Intervention							
IKMT + NRT	Δ (only IKMT)	○	○	○	○	Δ (only IKMT)	
IKMT	○	○	○	○	○	○	
Assessment							
Check symptoms and Med change	○	○	○	○	○	○	○
NRS for neck pain	○	○∗	○∗	○∗	○∗	○	○
VAS for neck pain		○∗	○∗	○∗	○∗	○	
Neck ROM		○∗	○∗	○∗	○∗	○	
NRS for arm pain		○∗	○∗	○∗	○∗	○	○
VAS for arm pain		○∗	○∗	○∗	○∗	○	
NDI		○		○†		○	○
SF-12		○		○†		○	○
PGIC				○†		○	○
PCL-5-K		○		○†		○	○
Adverse events		○	○	○	○	○	○

If Day 5 (visit 5) and day of discharge are the same, then the assessment for Day 5 (visit 5) could be replaced by discharge assessment. The follow-up visit at 12 wks after registration will have a time window of ± 14 days. F/U = follow-up, IKMT = integrative Korean medicine therapy, NDI = neck disability index, NRS = numeric rating scale, NRT = non-resistance technique, PCL-5-K = post-traumatic stress disorder checklist for DSM-5, PGIC = patient global impression of change, ROM = range of motion, SF-12 = 12-item short-form health survey, VAS = visual analogue scale.

∗ Additional evaluation after treatment.

† Investigate only if Day 4 ad 5 (visit 4, 5) and day of discharge are the same.

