### Statistical methods

2.11

In this study, both the intention-to-treat and per-protocol analyses will be performed, with intention-to-treat as the primary analysis. In the per-protocol analysis, participants who receive at least three sessions of treatment will be analyzed separately. The NRT + IKMT group and IKMT group will be compared, and the aim is to evaluate the superiority of NRT + IKMT.

Missing values will be processed through a mixed model for repeated measures in the primary analysis, and multiple imputations and the last observation carried forward will be performed for sensitivity analysis. For the Kaplan-Meier curve and log-rank test, the patients who drop out will be right censored, and regarding intermittent censoring, we will assume that no event occurred during the specified time period.

The sociodemographic characteristics of the participants and treatment expectancy will be evaluated by group. Continuous variables will be presented as mean (standard deviation) or median (quartile), and the two groups will be compared using the Student *t* test or Wilcoxon-rank sum test depending on the distribution pattern. Categorical variables will be presented as frequency (%) and will be analyzed using chi-square test or Fisher's exact test.

The endpoints of this clinical trial are the changes in the continuous outcomes (NRS, VAS, NDI, SF-12, ROM, PCL-5-K) at each time point from the baseline. A linear mixed model will be used as the primary analysis, and a random intercept model, which includes subject the random effects. Fixed effects will include baseline outcomes and clinically important covariant factors that are statistically significantly differ between groups at baseline as the covariates. In addition, time, group allocation, and the time and group interaction will be included in the model to examine the differences in the amount of change over time between the groups. For sensitivity analysis, we will perform analysis of covariance on the multiple imputations and last observation carried forward sets with the same covariates as those in the primary analysis and the group set as the fixed factor.

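### A Table 1 footnote lets a single, untimed discharge score stand in for the Day-5 post-treatment NRS, so for patients discharged on Day 5 the primary value may not be the defined measurement

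*Protocol article*

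**What the plan says.** The Abstract (Method) fixes the primary time point: "The primary outcome is a change in the numeric rating scale for neck pain immediately after treatment on hospital day 5", against baseline. Section 2.5.1 describes the scale but adds nothing on timing.

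In Table 1 (section 2.6), neck-pain NRS on Days 2 to 5 carries an asterisk, explained as "Additional evaluation after treatment". The discharge and 12-week cells have none. A footnote then says that if Day 5 and discharge coincide, "then the assessment for Day 5 (visit 5) could be replaced by discharge assessment".

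For the experimental arm, Table 1 lists IKMT + NRT on Day 5 and IKMT only at discharge. Section 2.3.1 says that "four sessions of NRT will be administered from hospital day 2 to 5".

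NDI, SF-12 and PCL-5-K are scheduled on Day 2, at discharge and at 12 weeks; PGIC at discharge and 12 weeks. All four also have a Day-4 cell with a dagger: "Investigate only if Day 4 ad 5 (visit 4, 5) and day of discharge are the same". The last visit is anchored to enrolment: "The follow-up visit at 12 wks after registration will have a time window of ± 14 days". Section 2.11 takes as endpoints the "changes in the continuous outcomes (NRS, VAS, NDI, SF-12, ROM, PCL-5-K) at each time point from the baseline".

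**The concern.** The primary measurement is defined by a day and by its position relative to that day's treatment. The footnote keeps the day but drops the position. It does not exempt the primary NRS, does not require the replacement to follow treatment, and is optional, so patients discharged on the same day may be handled differently.

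An analysis plan cannot repair this. A post-treatment score that was never taken cannot be recovered. The planned mixed model deals with missing values, but a replaced score enters as an observed Day-5 value.

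The lesser concern is the four questionnaires. Between baseline and 12 weeks their only unconditional assessment is at discharge, for which the document gives neither a day nor a window. If the arms leave at different times, the discharge comparison sets them side by side at different elapsed times.

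**Working it through.** **1. Table 1, Day 5 against discharge.**

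| Item | Day 5 | Discharge |
|---|---|---|
| Neck-pain NRS | scheduled, plus a post-treatment score | one score, no timing relative to treatment |
| Experimental arm | IKMT + NRT | IKMT only |
| NDI, SF-12, PGIC, PCL-5-K | none (Day-4 cell under the dagger) | scheduled |

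Three kinds of patient follow:

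- Discharged after Day 5: both visits occur separately and the primary score is as defined.
- Discharged on Day 5: the footnote applies. The score meets the definition only if it happens to be taken just after treatment. Table 1 does not say which intervention cell governs that day.
- Discharged before Day 5: no Day-5 score. The value is missing, but the NRS scores up to discharge are available to the model.

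**2. The dagger.** Day 4 and Day 5 cannot both be the day of discharge, so the condition as written is never met. Reading it as Day 4 *or* Day 5 makes it workable, but the Day-4 cell then still depends on the day of discharge. On either reading no questionnaire has an unconditional in-hospital follow-up on a fixed day.

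**3. The plan's own sample size (section 2.7).** Inputs: d = 0.63, correlation 0.5, two-sided alpha 0.05, power 90%.

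- Residual SD in units of the outcome SD: √(1 − 0.5²) = 0.866.
- Normal approximation: n = 2 × (1.960 + 1.282)² × 0.75 / 0.63² = 39.7, so 40 per group. The noncentral t gives 41, as stated.
- Withdrawal: 41 / 0.70 = 58.6, so 59, against 60 stated.

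Section 2.7 also gives a type 2 error of 0.2, which conflicts with 90% power; that is a separate matter. I use 90% with covariate adjustment because it reproduces 41, although 80% power without adjustment gives 40, so the match does not settle the conflict.

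**4. What replacement could cost: illustration only.** Let q be the share of patients whose Day-5 score is replaced (equal in both arms) and f the share of the between-arm effect missing from a replaced score. Neither is in the document. With 41 per group and unchanged SD:

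Power = Φ( 0.63 × (1 − q f) / 0.866 × √(41/2) − 1.960 )

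| q | f | Effective d | Power |
|---|---|---|---|
| any | 0 | 0.63 | 0.909 |
| 10% | 25% | 0.614 | 0.895 |
| 20% | 50% | 0.567 | 0.842 |
| 30% | 50% | 0.5355 | 0.799 |
| 30% | 100% | 0.441 | 0.635 |

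The first row is the case where every replacement score follows treatment.

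**The case against.** The strongest reply is that replacement occurs only when discharge falls on Day 5. The day is unchanged, and a score taken at discharge after that day's treatment is the defined measurement. This stands, and it limits the conclusion to *may not be*. It does not remove the point, because the text does not require that order.

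Four stronger readings are tempting and are not supported:

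- *Unblinded staff choose which score to use.* The footnote does not say who applies it, and section 2.9 assigns outcome measurement to a blinded assessor not involved in screening or intervention.
- *Discharge depends on recovery, so the timing is outcome-dependent.* This is plausible, but no discharge criterion is given. The document shows only that the discharge day is not fixed.
- *Patients discharged before Day 5 make the primary result missing not at random.* Section 2.11 uses a repeated-measures mixed model, and NRS is recorded before and after treatment on each earlier treatment day the patient attends. If early discharge follows improvement visible in those scores, the model accommodates it. Section 2.7 also allows 30% withdrawal.
- *The effect is diluted by a definite amount.* Assume 10–30% replaced, a missed drop of 0.5–1.0 NRS points in the NRT arm and SD 2. The dilution is then 0.10 × 0.5 = 0.05 to 0.30 × 1.0 = 0.30 points, or 4–24% of 0.63 × 2 = 1.26. All these inputs except d are assumed, and the sum counts a loss in one arm only. Controls are also treated on Day 5 and could lose their own post-treatment drop; only the difference between the arms matters.

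On the intervention cells, it can be said that the footnote replaces an assessment, not a treatment, and that the discharge cell may be meant for later discharges. That is a possible reading, but Table 1 does not state it.

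On the questionnaires, assessment at discharge is a common choice, these are secondary outcomes, and all four have a 12-week visit not tied to discharge. That makes this part minor.

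**Conclusion.** The point holds in a limited form. As written, the footnote allows an untimed discharge score to be recorded as the primary endpoint for patients discharged on Day 5. How many patients this concerns, and whether any effect is lost, cannot be derived from the document. The illustrated power runs from 0.909 (no loss) to 0.635 (30% replaced, all effect lost in them) and rests on assumed q and f, equal replacement in both arms and an unchanged SD. It deserves correction because it touches the primary measurement, cannot be repaired in analysis and costs almost nothing to remove.

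Two smaller points also stand. The dagger condition cannot be met as worded, and the only unconditional in-hospital post-baseline questionnaire time has no fixed day and may differ between arms. Table 1 and section 2.3.1 do not settle which intervention cell applies when Day 5 is the discharge day.

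**What to change.** - **Primary NRS.** Reverse the footnote: the pre- and post-treatment Day-5 NRS is always taken, including when Day 5 is the discharge day, and its values are copied to the discharge visit. Cost: one amended footnote and no added visit.
- **Discharge before Day 5.** Leave the missing Day-5 score to the planned mixed model. A telephone score on Day 5 should not be substituted, since it cannot be taken just after treatment and would add a second mode of measurement.
- **Questionnaires.** Reword the dagger so that it can be met. Then either collect NDI, SF-12, PGIC and PCL-5-K on one fixed in-hospital day, at the cost of a small added questionnaire burden, or name the 12-week visit as their main comparison, at no cost in data collection. In both cases treat discharge scores as descriptive.
- **Intervention cells.** Reconcile the Day-5 and discharge cells of Table 1 with section 2.3.1 for patients whose Day 5 is the discharge day. Which of them applies is for the investigators to state.

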### Blinding (masking)

2.9

Due to the nature of the intervention, it will be impossible to blind the participants and the physician, so we will blind the assessor, who is not involved in the screening or intervention, during the outcome measurements.

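### NDI, SF-12, PCL-5-K and PGIC have no fixed-day in-hospital follow-up value in Table 1, so their in-hospital group contrast, taken at discharge, is not at a common time

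*Protocol article*

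**What the plan says.** Section 2.6, Table 1, marks NDI, SF-12 and PCL-5-K at Day 2, Day 4 (with †), discharge and 12 weeks. PGIC has the same marks without Day 2. The Day 5 cells of all four are blank. The † footnote reads "Investigate only if Day 4 ad 5 (visit 4, 5) and day of discharge are the same". NRS and VAS for neck and arm pain, and neck ROM, are marked on each of Days 2 to 5.

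Two further notes bear on timing. When Day 5 is also the discharge day, "the assessment for Day 5 (visit 5) could be replaced by discharge assessment". For the last visit, "The follow-up visit at 12 wks after registration will have a time window of ± 14 days".

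Section 2.11 takes as endpoints "the changes in the continuous outcomes (NRS, VAS, NDI, SF-12, ROM, PCL-5-K) at each time point from the baseline", and states that "time, group allocation, and the time and group interaction will be included in the model". PGIC is not in that list. Section 2.9 says "it will be impossible to blind the participants and the physician". Section 2.3.1 places the four NRT sessions on hospital days 2 to 5.

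**The concern.** A randomised comparison is easiest to read when both arms are measured at the same time after randomisation. Discharge is not such a time. It happens after randomisation, its day can vary from patient to patient, treatment may change it, and patients and treating physicians know the allocation. Patients are admitted because of their neck pain (section 2.2.1), so a link between recovery and discharge is plausible.

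For these four instruments, discharge is the only in-hospital follow-up. A patient who stays beyond Day 5 has no score for disability, quality of life, stress symptoms or global change at the end of the NRT course. At stake is the short-term contrast on these secondary outcomes: a difference, or its absence, at discharge could reflect the treatment, the day of measurement, or both.

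**Working it through.** The point rests on no figure of the plan, so there is none to reproduce. The sample size in section 2.7 concerns the primary outcome and does not enter.

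**Step 1: the schedule (Table 1).**

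| Outcome | Day 2 | Day 3 | Day 4 | Day 5 | Discharge | 12 weeks |
|---|---|---|---|---|---|---|
| NRS neck, NRS arm | yes | yes | yes | yes | yes | yes |
| VAS neck, VAS arm, ROM | yes | yes | yes | yes | yes | no |
| NDI, SF-12, PCL-5-K | yes | no | † | no | yes | yes |
| PGIC | no | no | † | no | yes | yes |

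**Step 2: what † can deliver.** If both days must equal the discharge day, the condition is never met. If either may, the discharge column already calls for the forms on that day. If it were meant to require a Day 4 form from someone leaving on Day 5, it would depend on a discharge not yet known and would cover only those early leavers. On every one of these readings, a patient who stays past Day 5 has no fixed-day value.

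**Step 3: the analysis.** Section 2.11 does not say whether time is the visit label or the actual day. With the visit label, discharge is one level whatever its day. Using the actual day would not fully solve the problem: if patients leave because they have improved, the measurement time itself depends on the outcome.

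**Step 4: possible size, calculated by hand.** All inputs are assumptions, since the document gives no recovery rate or length of stay. Let the score be 25·exp(−k·t), with k = 0.10 per day (NRT) and 0.075 per day (control), and control discharge on day 8.

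- Both at day 8: 25·e^(−0.80) − 25·e^(−0.60) = 11.23 − 13.72 = −2.49.
- NRT one day earlier: 25·e^(−0.70) − 13.72 = 12.41 − 13.72 = −1.31, or 52% of −2.49.
- NRT two days earlier: 25·e^(−0.60) − 13.72 = 0, or 0%.
- NRT one day later: 25·e^(−0.90) − 13.72 = 10.16 − 13.72 = −3.56, or 143%.
- No true effect (k = 0.075 in both arms), one arm a day earlier: 25·e^(−0.525) − 13.72 = +1.07. A day later: 25·e^(−0.675) − 13.72 = −0.99.

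**Step 5: possible size, with variation between patients.** This simulation uses the same mean rates with lognormal spread (SD 0.4 on the log scale), baseline 25 (SD 5) and 400,000 patients per arm. Discharge time is w × (time to reach 60% of baseline) + (1 − w) × (a random stay with mean 8 days), limited to 3 to 21 days. The common day is day 7.

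| w (dependence on recovery) | Mean stay, NRT / control | Difference at discharge | Difference at common day | Share kept |
|---|---|---|---|---|
| 0 | 8.01 / 8.02 | −2.19 | −2.26 | 97% |
| 0.25 | 7.39 / 7.84 | −1.81 | −2.29 | 79% |
| 0.5 | 6.76 / 7.69 | −1.29 | −2.27 | 57% |
| 0.75 | 6.15 / 7.53 | −0.73 | −2.28 | 32% |
| 1 | 5.58 / 7.38 | −0.12 | −2.28 | 5% |

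**Step 6: a second assumed model.** Baseline NDI is 22 (SD 6), recovery is about 10% per day, and the NRT rate is 1.4 times as fast. The Day 5 difference is 1.9 points (d 0.49). At discharge it is 2.4 (d 0.51) if discharge is unrelated to recovery, 1.7 (d 0.38) if half of discharges follow recovery, and 1.0 (d 0.27) if all do.

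**Step 7: who must be covered on Day 5.** In a variant of the second model, with fully recovery-driven discharge allowed from Day 4, the Day 5 difference falls from 2.35 to 1.84 points (d 0.53 to 0.44) when only patients still in hospital are scored. Restricting the assessment to them conditions on the same event.

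**The case against.** The strongest objection is to any claim of direction. A reader might infer that the arms will be measured on different days and that a real NRT benefit is therefore understated. The document does not support this. It gives no discharge criteria, no expected stay, no account of who decides discharge, and no sign that discharge will differ by arm. Section 2.9 says only that patients and physicians cannot be blinded. Understatement needs two unstated conditions: discharge follows recovery, and NRT patients leave earlier. The illustrations agree: without the link, the first model shows almost no loss and the second shows a discharge contrast slightly larger than Day 5. The sizes also depend on whether the NRT effect continues after the last session. With unlinked discharge, a rerun of the second model gave 2.3 points if it continues and 1.4 if it stops. This objection stands in full.

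Second, the footnote is visibly garbled, and a negation may be missing. If the Day 4 forms were meant for patients not leaving then, a fixed in-hospital value would exist, though after at most three of the four NRT sessions. That possibility cannot be excluded. It does not rescue the text as printed, which sites cannot apply.

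Third, how time is coded is commonly left to an analysis plan that is not shown. That also stands, so the point rests on when the data are collected and not on the model.

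Fourth, the reach is limited. It would be wrong to say that every functional outcome is affected, because ROM is scored on Days 2 to 5.

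**Conclusion.** The concern holds as a statement about timing. As Table 1 is written, these four secondary outcomes have no fixed-day in-hospital follow-up value, and their in-hospital group contrast is not at a common time after randomisation.

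The direction and size of any bias are unknown. It may be an understatement, close to nil, or an overstatement, depending on facts about discharge that the document does not give. The 97% to 5% range, the 143% and the roughly ±1 point under no effect show only what is possible under assumed recovery and discharge patterns. They are not estimates for this trial.

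The Day 5 primary outcome, the 12-week values of the same four instruments and cervical ROM are untouched. This is a cheap improvement, not a threat to the main conclusion.

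**What to change.** - Correct the † footnote, or delete it together with the Day 4 marks.
- Mark NDI, SF-12, PCL-5-K and PGIC at Day 5 (visit 5) for all randomised patients, using telephone or a form for anyone already discharged.
- Make Day 5 the in-hospital group contrast for these four outcomes.
- Report the discharge values descriptively, with length of stay by arm.
- Leave the 12-week assessment as it is.

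The cost is an edit to four rows of Table 1 and its footnote, a few more minutes of questionnaires at a visit that already takes place (section 2.5.2.6 puts the SF-12 at about 5 minutes), and occasional contact with patients who left before Day 5.
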